### Objectives {7}

The primary objective of the present study is to determine if different exercise types produce varied outputs on CPM in a subgroup of CLBP patients classified as having CS pain. The secondary objectives are to evaluate if a 12-week exercise intervention program would alter executive functioning, QoL, disability, and pain and to examine the relationship between patient characteristics, executive functions, CPM, and QoL in CLBP patients.

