### Primary outcome measure

#### CPM

The CPT will be used to measure CPM. For the conditioning stimulus, the participants’ non-dominant hand will be immersed in a bucket with temperature-controlled cold water (1 °C–4 °C), monitored by a thermometer for up to 1 min. The participant has to remain with the hand immersed in water without making muscle contractions or changes in position. Withdrawal from the water will be allowed if the patient can no longer tolerate the painful stimulus. This test will be conducted in a room with controlled room temperature, humidity, lighting, and noise.

Using a digital pressure algometer, the pressure pain threshold (PPT) will be performed in the forearm regions and tibialis anterior muscle of the dominant limbs before and after 1 min of the CPT. The tibialis anterior muscle and the distal part of the dorsal forearm, which had not been immersed in water, will be evaluated because of the lack of their relationship with the participants’ musculoskeletal complaints.

The operation of the pressure algometer and PPT measurement will be explained to the patients, and a practice test will be conducted on the patients’ dominant forearm to ensure that the test has been understood. Force will gradually be increased [1 kg-force/s] until the feeling of pressure changes to pain. The PPT will be recorded in kilograms force [Kgf]. The PPT will be repeated three times and the mean will be calculated to give the baseline PPT. The efficiency of the descending nociceptive inhibitory system will be evaluated by calculating the difference between PPT values in CPT (final cost − initial value) [41].

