### Statistical methods

#### Statistical methods for primary and secondary outcomes {20a,b}

The Shapiro–Wilk test will be used to assess the normality of the distribution of the data. A one-way analysis of variance (ANOVA) will be used to compare baseline characteristics between the groups. Descriptive statistics will be used to calculate the mean values of all outcome variables collected. A repeated measure ANOVA statistic will be used to evaluate the effect of three types of exercise interventions on CPM, neurophysiological outcomes, pain, disability, strength measures, and QoL. The study will use a 5 (between subjects – type of exercise interventions: AE vs. MCE vs. SS vs. patient education vs. no-pain control) × 3 (within subjects – time: before vs. after vs. 3 months after the intervention) mixed design. Tukey’s post hoc analysis will be conducted to establish differences between the groups. Effect size will be estimated by dividing the mean difference in outcomes between the intervention and control groups by the combined standard deviation of the two groups [56].

The primary outcome will undergo a per-protocol analysis. Pearson correlation analysis will be performed to determine the relationship between patient characteristics (Table 4), CPM, executive functioning, pain, strength measures, disability, and QoL. Multiple linear regression analysis will be used to deduce the characteristics of individuals responding positively to exercise interventions. For all measurements, *p* will be considered significant, if it is < 0.05. The data collected will be analyzed using SPSS (Statistical Program for the Social Sciences) 16.0 (IBM Corp., Armonk, NY).

**Table 4 Tab4:** Summary of patient characteristics to be collected

Characteristics	CLBP group	Control group
Age (years)	X	X
Gender (male/female)	X	X
Pain episode duration (weeks)	X	X
Body mass index (kg/m^2^)	X	X
Education level (yes/no; school incomplete, completed secondary school, completed diploma/completed bachelors and above)	X	X
Employment status (yes/no; employed (full or part-time), unemployed, retired)	X	X
Marital status (yes/no; married/separated/ divorced, single)	X	X
Personal behaviors Alcohol status (yes/no) Smoking status (yes/no)	X	X
Comorbidities	X	X
Fear avoidance behavior	X	X
Perception of improvement	X	X

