## Discussion

Although physical exercises have been considered as the foundation of management of musculoskeletal pain conditions with proven benefits [63], the precise mechanisms underlying the effects remain unclear [64]. Traditional explanations based on biomechanics and corresponding changes in loading of the musculoskeletal system regarding why exercise improves pain and disability in chronic musculoskeletal pain fail to consider the complete biopsychosocial spectrum of factors [65]. Exercise prescription is usually based on the preferences and expertise of the individual clinician. Because exercise prescription directly impacts intervention outcomes, analyzing the exercise parameters in patients along the chronic pain spectrum is crucial.

The study will offer the following benefits. First, it will help in acquiring more information and evidence about exercise-induced analgesia from the CPM perspective. Second, investigating the relationship between executive functions, CPM, and QoL will provide further inputs for high-quality randomized controlled trials in the future. Third, measuring the outcomes of exercises will help in scientifically prescribing different exercise types. The study outcomes will also help in identifying the characteristics of individuals responding or responding indifferently to exercises; this will avoid wastage of health resources or assist in directing the non-responsive individuals to other alternative interventions.

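### A broad set of Pearson correlations is judged at unadjusted p < 0.05, with no multiplicity control and no exploratory label, so chance findings are close to certain

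*Protocol article*

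**What the plan says.** All references are to the protocol article.

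- **Objectives {7}.** One of the secondary objectives is "to examine the relationship between patient characteristics, executive functions, CPM, and QoL in CLBP patients".
- **Statistical methods for primary and secondary outcomes {20a,b}.** The analysis is "Pearson correlation analysis will be performed to determine the relationship between patient characteristics" (those of Table 4), and the sentence goes on to "CPM, executive functioning, pain, strength measures, disability, and QoL. Multiple linear regression analysis will be used". The last words of that quote open the next sentence, which gives the task of characterising responders to a separate regression.
- **Same section, significance rule.** For all measurements, p "will be considered significant, if it is < 0.05". The correlations are not exempted.
- **Same section, multiplicity.** "Tukey’s post hoc analysis will be conducted to establish differences between the groups". No procedure is named for the correlations.
- **Table 4**, titled "Summary of patient characteristics to be collected", has 11 rows. One of them holds both alcohol and smoking status.

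**The concern.** A single per-test threshold is applied to a large grid of characteristic-by-outcome correlations. The statistical section does not say which correlations carry the objective and does not separate them from the rest. Under that rule some correlations will be declared significant even if nothing is related to anything.

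What is at stake is the credibility of a declared secondary objective. The Abstract lists these relationships among the trial's objectives, and the Discussion presents the executive function, CPM and QoL relationships as input for later trials. Chance results labelled significant would then be carried into the design of those trials. The problem lies in the error rate of the whole set, so it arises whichever correlation coefficient is used.

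**Working it through.** **The plan's own figures.** The protocol states no number of correlations and no error rate for them, so there is no figure on this point to reproduce. Its one design calculation (30 per group, difference 80 kPa, SD 100 kPa, two-sided 0.05) concerns the group comparison. It reproduces at 87.3% by the normal approximation, against the stated 87%. It has no bearing on the correlations.

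**Inputs**

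- Characteristics: 11 (rows of Table 4), or 12 if alcohol and smoking are counted separately.
- CPM: 1 score, or 2 if the sites are kept apart, since the pressure pain threshold "will be performed in the forearm regions and tibialis anterior muscle of the dominant limbs".
- Executive function: 2 (letter-number sequencing, Stroop interference).
- Pain: 1 (NPRS). Disability: 1 (ODI).
- QoL: 4 WHOQOL-BREF domain scores.
- Strength: 6 muscle groups (text of the strength section).
- Outcome variables in total: 1 + 2 + 1 + 1 + 4 + 6 = 15.
- Per-test threshold: 0.05.
- Time points: the protocol has three and does not say which is used here. One is assumed.

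**Formulas.** Pairs m = characteristics × outcome variables. Expected false positives if every null is true = 0.05 × m, which holds whether or not the tests are independent. Chance of at least one = 1 − 0.95^m, which assumes independent tests.

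| Way of counting | m | Expected false positives | Chance of at least one |
|---|---|---|---|
| One score for each of the 6 domains | 11 × 6 = 66 | 3.3 | 96.6% |
| Objective only: CPM 1, executive 2, QoL 4 | 11 × 7 = 77 | 3.9 | 98.1% |
| All 15 outcome variables | 11 × 15 = 165 | 8.3 | 99.98% |
| Alcohol and smoking separate, CPM sites separate | 12 × 16 = 192 | 9.6 | 99.99% |

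**Outcome-by-outcome pairs.** The sentence also covers correlations among the outcomes themselves. With 15 variables these add 15 × 14 / 2 = 105, giving 165 + 105 = 270 tests and 270 × 0.05 = 13.5 expected. The CPM, executive function and QoL associations that the objective names are of this kind.

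**Dependence.** The outcomes will be correlated with each other. A simulation of the 165-pair case (120 participants, independent characteristics, equally correlated outcomes) leaves the expected number at about 8. The chance of at least one false positive falls to about 99% at a correlation of 0.5 between outcomes and to about 93% at 0.8. Dependence would lower it for the smaller counts too.

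**The case against.** The strongest reply has four parts.

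1. **The count is not the protocol's.** This stands. The figure of 165 depends on how domains are scored. The objective itself covers only 77 of those pairs. The other 88 (11 × 8, for six strength scores, pain and disability) come from the statistical section alone. The result must therefore be given as a range.

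2. **The global null is a worst case.** This stands too. The Background describes CPM as related to cognitive performance and QoL, and the Study strengths section cites a decline in CPM with age. If some associations are real, fewer false positives are expected. Nor does the protocol promise a 5% error rate for the whole set. Its 0.05 is a per-test threshold, so no stated figure is contradicted.

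3. **The protocol is already modest about these results.** This stands in part. The Abstract and Discussion speak of informing future trials, the Background uses the language of exploration, and the objective does single out executive functions, CPM and QoL. But the statistical section, which governs what is reported as significant, applies the same rule to every correlation.

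4. **A SAP could settle this.** It could add key pairs or an adjustment, and the absence of such detail would be no finding. The point is narrower: the protocol states a rule that, read as written, includes the correlations.

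A reader might also infer that patients will be redirected on the strength of these correlations, because the Discussion expects the results to "assist in directing the non-responsive individuals to other alternative interventions". The document does not support that. The Discussion ties redirection to the characteristics of responders, and the statistical section assigns those to multiple linear regression. It is also an expected benefit, not a decision rule. The regression falls under the same 0.05 rule, but the pair counts above do not describe it.

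**Conclusion.** The concern holds as a minor to moderate point about a secondary analysis. Applied as written, the rule would almost surely report some chance correlations as significant. With no true association, about 3 to 10 false positives are expected over 66 to 192 characteristic-by-outcome pairs, and about 4 within the stated objective. The chance of at least one is about 97% or more under independence.

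These figures assume one time point and the variable counts listed above. The expected numbers shrink to the extent that real associations exist, and the chance of at least one falls with correlated outcomes. The primary between-group comparison of CPM and the sample size are untouched.

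**What to change.** In the section on statistical methods for primary and secondary outcomes:

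- Name the associations that the Abstract, Objectives and Discussion single out: CPM with letter-number sequencing, with Stroop interference and with each of the four WHOQOL-BREF domains. With one CPM score that is 1 + 1 + 4 = 6 tests. State the time point, and adjust this small set, for example by Holm (smallest p-value compared with 0.05 / 6 = 0.0083).
- Label all other correlations exploratory, and report estimates with confidence intervals and Benjamini-Hochberg q-values.
- State that the unadjusted 0.05 rule does not apply to the correlations.

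Holm and Benjamini-Hochberg are one workable choice among several. The essential elements are the named set and the exploratory label.

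The cost is wording and one adjustment step, with no change to data collection or sample size. The downside is that fewer correlations will be called significant.

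### Pearson correlation is named for every Table 4 characteristic, but employment status has three unordered levels, so its coefficient and p-value depend on arbitrary codes

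*Protocol article*

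**What the plan says.** Under Objectives {7}, one secondary aim is "to examine the relationship between patient characteristics, executive functions, CPM, and QoL in CLBP patients". The Abstract lists the same relationship as its third objective.

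The method is given under Statistical methods for primary and secondary outcomes {20a,b}: "Pearson correlation analysis will be performed to determine the relationship between patient characteristics (Table 4", together with CPM, executive functioning, pain, strength, disability and QoL. The significance rule in that section is general: "For all measurements, *p* will be considered significant, if it is < 0.05".

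Table 4 mixes several types of variable:

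- Continuous: age, pain episode duration, body mass index.
- Binary: "Gender (male/female"; "Personal behaviors Alcohol status (yes/no) Smoking status (yes/no".
- Ordered: "Education level (yes/no; school incomplete, completed secondary school, completed diploma/completed bachelors and above".
- Unordered with three levels: "Employment status (yes/no; employed (full or part-time), unemployed, retired".
- Unordered, number of levels unclear: "Marital status (yes/no; married/separated/ divorced, single".
- No scale stated: comorbidities, fear avoidance behavior, perception of improvement.

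The section names no other measure of association, no indicator coding, and no restriction of the correlation to the quantitative items. The multiple linear regression in the same section has a different purpose, namely to describe who responds to exercise.

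**The concern.** Pearson's r measures how closely one numeric variable follows a straight line in another. An unordered factor with three or more levels has no numeric values until someone assigns codes, and nothing in the data says which level should be 1, 2 or 3. Exchanging two codes is not a linear change, so it alters the size of r, and its p-value, as well as the sign. A reader would then take the result as showing that employment is, or is not, related to CPM or QoL when it partly reflects the data-entry form. The same holds for marital status and comorbidities if they are stored as unordered category codes. At stake is part of a secondary objective that the Discussion expects to inform later trials.

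**Working it through.** **The plan's own figure.** The article gives no computed figure for the correlation analysis. Its only design calculation reproduces: 30 per group, a difference of 80 kPa and an SD of 100 kPa give 87.3% power by the normal approximation and 86.1% by the exact t calculation, against the stated 87%. Then 30/0.70 = 42.9, rounded up to 43, and 4 × 43 = 172 patients. Only the 172 is used below.

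**Assumptions.** The article gives no category shares or outcome means by category, so both are assumed: 103 employed, 43 unemployed and 26 retired (total 172), with outcome means 0, −0.5 and +0.2 and a within-category SD of 1.

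**Quantities that do not depend on codes.** The shares are 0.599, 0.250 and 0.151.

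- Overall mean = 0.250 × (−0.5) + 0.151 × 0.2 = −0.0948.
- Between-category variance = 0.250 × 0.25 + 0.151 × 0.04 − 0.0948² = 0.0596.
- Total variance = 1 + 0.0596 = 1.0596.
- eta² = 0.0596/1.0596 = 0.0562, so eta = 0.237 under any coding.

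**Pearson's r for each coding.** With codes c and outcome y, r = cov(c, y)/√(var(c) × 1.0596), and t = r√170/√(1 − r²) on 170 degrees of freedom.

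| Codes (employed, unemployed, retired) | cov | var(c) | r | p |
|---|---|---|---|---|
| 1, 2, 3 | −0.0122 | 0.5496 | −0.016 | 0.84 |
| 1, 3, 2 | −0.1581 | 0.7272 | −0.180 | 0.018 |
| 2, 1, 3 | +0.1459 | 0.3914 | +0.227 | 0.003 |

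The other three codings are these in reverse, with the sign flipped and the same p. So one data set yields a clearly null result or a clearly significant one.

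**Range over other assumptions**, again with 172 patients and within-category SD 1:

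- Three nearly equal groups (58/57/57), means 0, −0.5, 0: |r| from 0.001 (p = 0.99) to 0.198 (p = 0.009); eta 0.229.
- Four levels (80/20/20/52), means 0, −0.5, −0.5, +0.1: |r| from 0.009 (p = 0.90) to 0.208 (p = 0.006); eta 0.226.
- Two levels (86/86), means 0 and 0.4: |r| = 0.196 and p = 0.0099 under either coding, the same p as the two-sample t-test. Only the sign changes.

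The last case marks the limit of the problem. Any recoding of a two-level item is a linear change, so |r| and p stay fixed.

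**The case against.** The strongest reply is that few items are touched.

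- Continuous items raise no coding question, and binary items keep |r| and p. Education is ordered, so its difficulty is the spacing of its levels. That calls for a rank measure, but it is not arbitrary labelling. All of this stands.
- In the education row, commas appear to separate levels and a slash joins alternatives within one. Read the same way, marital status has two levels and is safe. Comorbidities could be a count. This also stands, so only employment is clearly affected as listed.
- Education, employment and marital status each begin with yes/no, which could mean that they are collapsed to binary variables. That would remove the problem even for employment. But several categories follow and no collapsing rule is given, so the reading is possible and not established.
- Coding details are commonly left to an analysis plan. This is true, and their absence is not the complaint. The article itself names one method and the full list of variables it applies to, and the two do not fit.

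Two stronger readings are tempting, and the document supports neither. The first is that all coefficients for this objective are coding artefacts. They are not: the pairings among CPM, executive function, pain, strength, disability and QoL do not involve category codes at all. The second is that no-pain volunteers will be pooled with patients, creating correlations from the gap between the groups. Table 4 does have a control column, and the statistical section does not repeat the restriction, but Objectives {7} limits this aim to CLBP patients. A collection table does not define an analysis set, and nowhere does the article say that controls enter the correlation.

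**Conclusion.** The point holds in a narrow form and is minor. As written, the method does not suit employment status, nor marital status or comorbidities if these are coded as unordered categories. For such an item the conclusion at 0.05 can reverse with the coding alone, as p = 0.84 against 0.003 shows. Those p-values rest on assumed shares and means; the dependence on codes is algebraic and does not. How far the results would move in the trial depends on the actual category means, and the swing would be small if these hardly differ. The primary CPM comparison and the stated success criteria do not use this analysis.

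**What to change.** Replace the single method with a choice by variable type:

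- Pearson for continuous and binary characteristics.
- Spearman for ordered ones such as education.
- For unordered characteristics with three or more levels, one-way ANOVA with eta-squared, or a linear model with indicator variables and reported mean differences.

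In Table 4, state the levels of marital status and the scale of comorbidities. If the yes/no prefix means that education, employment and marital status are analysed as two-level variables, state the collapse for each; Pearson can then stay for those items.

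The cost is a few lines of wording and slightly more output. No extra data or participants are needed, and the sample size does not change. The rule should be set before the association analyses are run.

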#### Letter–number sequencing subtest

The letter–number sequencing subtest in WAIS-III will be used to evaluate working memory. In this task, the participants need to listen to a series of alphanumeric characters and repeat the characters back verbally in a specific order (numbers first in the ascending order, followed by letters in the alphabetical order). The test items will be presented in the same order for all participants. The researcher will read the test items aloud, at approximately 1 s per character. The participants will be asked to record their responses by speaking aloud to the researcher, and the researcher will mark the test stimuli as completely correct or incorrect. This subtest involves 21 items. The outcome is expressed as a scaled score; each correct response shall receive 1 point, and the maximum possible score is 21 [42].

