#### Stroop neurophysiological test

The test stimuli will be presented on a computer screen. A total of 40 items will be presented in 8 rows of 5 items each. The items and the print colors will appear in a random order. The first subtask will show color words in a random order (red, blue, yellow, and green) printed in black ink. The second subtask will display solid color patches in one of these four basic colors. In the third subtask, the color words will be printed in an incongruous ink color. For example, the word *yellow* will be printed in red ink. The participants will be allowed to identify the colors in English/Hindi. No time limit will be assigned to complete a subtask. The time required in seconds to complete each Stroop subtask will be recorded using a stop clock (Stroop I, Stroop II, and Stroop III) [43]. The interference score is determined by subtracting the mean score of the first and second subtest from the amount of time required to complete the third subtest.

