The results will be considered clinically significant if a minimum difference of 10% change in PPT values in CPT is maintained at 6 months. Based on a previous study results [57] and a standardized mean score of 10 [58] on the letter–number sequencing subtask of WAIS-III, the mean reaction time for the Stroop interference effect will be fixed at approximately 230 s for the treatment to be considered successful. A reduction of 2 points on the NPRS [59], a cut-off value of 13, and a difference of 8 and 4 points will be considered as the minimal clinically important difference for the ODI [60], WHOQOL-BREF [61], and isometric muscle strength [62] respectively, which would indicate the success of the therapeutic intervention used.

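### The 230 s Stroop success level does not fit the Stroop score the protocol defines, and it is a fixed level where the endpoint is a change from baseline

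*Protocol article*

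**What the plan says.** All references are to the protocol article.

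**Stroop scoring (Stroop neurophysiological test).** "A total of 40 items will be presented in 8 rows of 5 items each". "The time required in seconds to complete each Stroop subtask will be recorded using a stop clock". The interference score comes from "subtracting the mean score of the first and second subtest from the amount of time required to complete the third subtest". Also, "No time limit will be assigned to complete a subtask".

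**Stroop success criterion (Statistical methods {20a,b}).** For a treatment to count as successful, "the mean reaction time for the Stroop interference effect will be fixed at approximately 230" seconds. The sentence gives a cited study as its basis, together with "a standardized mean score of 10" on letter–number sequencing. It states no direction, no baseline reference and no comparator.

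**Endpoint definition (Outcomes {12}).** The number sequencing and Stroop tests are secondary endpoints, defined as change from baseline to weeks 12 and 24.

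**Letter–number sequencing scoring.** The section first calls the outcome a scaled score, then gives a counting rule: "each correct response shall receive 1 point, and the maximum possible score is 21". It describes no conversion from count to scaled score.

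**The concern.** The success criterion and the outcome definition do not describe the same quantity. A mean reaction time is ordinarily a per-response measure, but the trial records no reaction times, only completion times for whole subtasks. If 230 s is carried over to the recorded score, it implies a very large interference effect.

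The criterion is also a fixed level. A participant or an arm can meet it before any treatment, so meeting it shows neither improvement nor benefit over education alone. Other criteria in the same paragraph are framed differently: the pain criterion is a reduction, and those for quality of life and muscle strength are differences.

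At stake is whether an intervention is called successful on executive functioning, the first-named of the secondary objectives. A threshold that nearly everyone or nearly no one meets gives that label no information.

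Letter–number sequencing raises a smaller, related problem. The reader cannot tell whether a raw count or a scaled score will be analysed, or what role the value 10 plays.

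**Working it through.** **Inputs from the protocol.** 40 items per subtask (8 × 5); subtask totals T_I, T_II and T_III in seconds; success value about 230 s. The value is taken from a cited study and cannot be reproduced from anything in the protocol, so the check is whether it fits the defined score.

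**Formula.** Interference = T_III − (T_I + T_II)/2.

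**Step 1: extra time per item at the threshold.** 230/40 = 5.75 s on every item of subtask III, over and above the average for subtasks I and II.

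**Step 2: how long subtask III would have to last.** The protocol gives no naming speed, so 0.5 to 3 s per item on subtasks I and II is assumed. The required T_III is 230 + 40 × (seconds per item).

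| Assumed s/item, I and II | Mean of T_I, T_II (s) | T_III for 230 s interference (s) | Ratio of T_III to the I/II mean |
|---|---|---|---|
| 0.5 | 20 | 250 | 12.5 |
| 1 | 40 | 270 | 6.75 |
| 2 | 80 | 310 | 3.9 |
| 3 | 120 | 350 | 2.9 |

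**Step 3: what interference would arise.** Assume that T_III is 1.5 to 3 times the I/II mean. Interference is then (multiple − 1) × the I/II mean:

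- 0.5 s/item: 10 to 40 s
- 1 s/item: 20 to 80 s
- 2 s/item: 40 to 160 s
- 3 s/item: 60 to 240 s

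Only the extreme corner (3 s per item and a threefold slowing) passes 230 s.

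**Step 4: direction.** Lower interference is better, so at or below 230 s is the natural reading, and nearly every participant would meet it at every visit. Read as at or above 230 s, almost none would. The level does not discriminate either way.

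**Step 5: level against change.** Outcomes {12} defines a change from baseline, and the criterion refers to no baseline. The two cannot be the same assessment.

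**Letter–number sequencing.** On the counting rule, 10 is 10/21 = 48% of items correct. As a standardized mean, it is the average of the reference population. These are different standards, and the text does not say which scale applies.

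**The case against.** **The comparisons are planned properly elsewhere.** This stands. The endpoint is defined as change, and Statistical methods {20a,b} plans a repeated-measures ANOVA with Tukey comparisons and effect sizes. The 230 s value enters none of these, nor the sample size calculation. That limits the consequence but does not repair the criterion.

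**Mean may refer to a group average, with reaction time used loosely for the interference score.** This is possible, but it does not help: an arm's average would then have to lie around 5.75 s of extra time per item.

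**The naming speeds are assumed.** This stands. The subtasks have no time limit, and the Background cites longer processing time in chronic low back pain. A reader might infer that interference cannot exceed some ceiling such as 80 s, or that everyone must pass. The protocol supports neither: it sets no upper bound and no direction. Eligibility requires a Mini-Mental State Examination score above 24, but that gives no response time. What holds is that results near 230 s would be rare over a wide range of assumed speeds.

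**The figure might be milliseconds per item.** A reader might infer this. For illustration, 0.23 s × 40 = 9.2 s on the defined scale, 25 times smaller than 230 s. The protocol does not say so, and the cited study is not available here, so a unit slip remains a possibility only.

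**The value 10 may not be a threshold.** This also stands. A reader might take it as a pass mark set against a raw count. Grammatically, the sentence offers 10 as part of the basis for the Stroop value, and the test's own section uses the scaled-score label, which fits a standardized 10. The supportable point is narrower: a scaled label with a raw-count rule in one section, and an unclear use of 10 in another.

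**Conclusion.** The Stroop success criterion is wrong as written. It names a quantity the trial does not record. Applied to the score that is recorded, it requires 5.75 s of extra time per item, and subtask III would have to take 2.9 to 12.5 times as long as subtasks I and II. This rests on an assumed 0.5 to 3 s per item. Under that assumption, and a subtask III time of up to three times the others, the cut-off separates almost no one in either direction. On the at-or-below reading, education alone would be labelled successful without any change.

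The conflict between a fixed level and a change-from-baseline endpoint needs no assumption.

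The letter–number sequencing point is secondary: the analysed scale and the role of 10 are unclear. The documents do not establish that 10 is a pass mark.

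The effect is confined to the success label for secondary outcomes. The planned ANOVA and the sample size are untouched.

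**What to change.** 1. Check the Stroop value against the cited study: which quantity, which unit, and per item or per subtask.
2. Unless it can be validly expressed in interference seconds as the Stroop section defines them, with a stated direction, remove the 230 s cut-off. Judge Stroop success by the between-arm difference in change from baseline in interference seconds, at the time points already named in Outcomes {12}.
3. For letter–number sequencing, state in both places whether the raw count (maximum 21) or a scaled score is analysed and, if scaled, how it is obtained. Say what the 10 is for, and do not use it as a fixed success level.

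The cost is a paragraph of wording. No new data, visits or participants are needed, because the subtask times are already collected at baseline and at follow-up.
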